# An explorative single-arm clinical study to assess craving in patients with alcohol use disorder using Virtual Reality exposure (CRAVE)—study protocol

**DOI:** 10.1186/s12888-023-05346-y

**Published:** 2023-11-14

**Keywords:** Virtual Reality, Alcohol Use Disorder, Cue Exposure Therapy, Craving, Psychophysiological parameters, Heart rate variability, Electrodermal activity, Pupillometry

## Abstract

**Background:**

Alcohol use disorder (AUD) belongs to the most burdensome clinical disorders worldwide. Current treatment approaches yield unsatisfactory long-term effects with relapse rates up to 85%. Craving for alcohol is a major predictor for relapse and can be intentionally induced via cue exposure in real life as well as in Virtual Reality (VR). The induction and habituation of craving via conditioned cues as well as extinction learning is used in Cue Exposure Therapy (CET), a long-known but rarely used strategy in Cognitive Behavioral Therapy (CBT) of AUD. VR scenarios with alcohol related cues offer several advantages over real life scenarios and are within the focus of current efforts to develop new treatment options. As a first step, we aim to analyze if the VR scenarios elicit a transient change in craving levels and if this is measurable via subjective and psychophysiological parameters.

**Methods:**

A single-arm clinical study will be conducted including *n* = 60 patients with AUD. Data on severity of AUD and craving, comorbidities, demographics, side effects and the feeling of presence in VR will be assessed. Patients will use a head-mounted display (HMD) to immerse themselves into three different scenarios (neutral vs. two target situations: a living room and a bar) while heart rate, heart rate variability, pupillometry and electrodermal activity will be measured continuously. Subjective craving levels will be assessed before, during and after the VR session.

**Discussion:**

Results of this study will yield insight into the induction of alcohol craving in VR cue exposure paradigms and its measurement via subjective and psychophysiological parameters. This might be an important step in the development of innovative therapeutic approaches in the treatment of patients with AUD.

**Trial registration:**

This study was approved by the Charité—Universitätsmedizin Berlin Institutional Review Board (EA1/190/22, 23.05.2023). It was registered on ClinicalTrials.gov (NCT05861843).

**Supplementary Information:**

The online version contains supplementary material available at 10.1186/s12888-023-05346-y.

## Background

Alcohol use disorder (AUD) is a severe disorder leading to a substantial burden of disease with worldwide 3 million deaths per year [1]. Current treatment approaches yield unsatisfactory long-term effects with relapse rates up to 85% [2]. Both the individual and their environment are strongly affected by the disorder. Including all cost components (direct and indirect cost estimates of e.g., health care, unemployment or premature mortality) associated to harmful alcohol use, the costs would equal about 2,6% of the Gross Domestic Product (GDP) in the examined countries [3]. Alcohol craving as the strong desire to drink, is a major predictor for relapse and a main diagnostic criterion [4, 5]. Craving is associated with psychological and physiological responses [6] and can be intentionally induced by confronting patients with alcohol-related cues according to the cue-reactivity paradigm [7], such as a bar or a glass of wine.

The intentional presentation of such conditioned, contextualized cues is used as part of „Cue Exposure Therapy “ (CET) in Cognitive Behavioral Therapy (CBT), aiming to enable patients to identify and handle individual relapse risks [8]. Cue Exposure Therapy has shown substantial clinical effects, although recent meta-analyses emphasized the small number and questionable quality of existing trials [9, 10]. Although it is an effective strategy, CET for patients with AUD has not yet been established in clinical routine, because of the high organizational, timely and financial costs [8]: a) actors need to be available, b) to assure realistic settings, real bars have to be visited or laboratory-based bars have to be created and c) the change between different contexts is limited [11]. Virtual Reality (VR) is a new technology that is currently developing rapidly across several fields, and VR-based therapies are about to become a major component of digital mental health [12, 13]. Using e.g., head-mounted displays (HMD) patients can immerse into a computer-generated 3D world, where realistic spatial and social interactions are possible in real-time [14]. VR interventions can be used for both therapeutic and diagnostic approaches and have been established for various psychiatric indications such as anxiety disorders (e.g., specific phobias, social anxiety disorder) and post-traumatic stress disorder. [13, 15]. Innovative approaches including virtual avatars in the therapy of psychotic disorders show promising results [12]. Furthermore, VR applications have received increasing attention in the field of substance use disorders (SUD) [16, 17]. VR yields several advantages compared to in vivo exposure: it enhances practicability of CET, allows comparability between treatment providers and offers high ecological validity by using multimodal dynamic stimuli in an immersive environment [15, 18].

The assessment of craving in VR paradigms can provide a basis for the development of an effective exposure therapy, allowing to understand which contextual cues elicit pronounced cue reactivity and should therefore be used for habituation and extinction learning in cue exposure therapy. Additionally, craving assessment can serve as an individually tailored diagnostic tool helping to identify high-risk situations and automatic responses. Studies on craving assessment in patients with AUD show that different alcohol-associated VR-scenarios successfully induce craving [17]. Interestingly, a recent study showed that craving was significantly related to the sense of presence, meaning the perceived ecological validity of the virtual environment, underlining the importance of a realistic, high-end 3D VR environment [19]. However, apart from one study using electroencephalography (EEG, [20]) only subjective craving parameters (e.g., visual analogue scales, VAS) were used [16]. VAS are the international standard but have several disadvantages: They rely on subjective reports and the assumption that patients with AUD can perceive and specify their own craving. VAS are also biased with respect to social desirability, meaning that individuals may not answer completely truthfully, but with respect to what is socially acceptable.

Psychophysiological parameters of craving (e.g., changes in electrodermal activity, pupil size and heart rate) are well established in studying physiological cue reactivity [6]. A recent meta-analysis confirmed the link between cue-induced craving and psychophysiological cue reactivity to alcohol use and relapse [7]. Considering specific physiological parameters, a review with 33 included studies confirmed the association between reactive HRV to alcohol cues and craving, faster relapse and negative mood [21]. High frequency HRV (HF-HRV), which reflects parasympathetic activity, has been shown to be increased by alcohol-related cues [22, 23]. Furthermore, a pilot study assessing pupil reactivity to alcohol-related and neutral cues as a predictor for relapse, showed that alcohol-dependent patients reacting with greater pupillary dilation were more prone to relapse at a 4-month follow-up [24].

Apart from one older study which examined electroencephalographic correlates of craving in a small cohort of 20 patients [20], physiological parameters have not been used as outcomes for VR-exposure in patients with AUD, yet [16]. In VR-studies on methamphetamine use disorder physiological data (heart rate variability, eye tracking, electrodermal activity) were able to discriminate between patients and healthy controls [25, 26].

The planned study we present here, aims to assess if VR exposure can induce craving, being intentionally induced by different VR scenarios, with help of subjective and objective parameters.

### Primary hypothesis

We hypothesize that exposure to alcohol-related scenarios in VR will elicit a transient increase in craving in patients with AUD, measurable with subjective and physiological parameters compared to exposure in a neutral VR environment.

### Exploratory objectives:

To identify VR-contextual cues predictive of pronounced cravingTo assess craving duration over the first 3 h following the exposureTo examine the influence of the sense of presence in VR on craving levelsTo assess motion sickness and its correlation to craving

## Methods and analysis

### Study design

This is a prospective, explorative, single-arm, study that will be conducted in the Psychiatric University Hospital Charité at St. Hedwig-Hospital, Berlin. Second participating recruitment site is the Salus Clinic Lindow. The study is approved by the Ethic committee of the Charité—Universitätsmedizin Berlin (EA1/190/22).

### Recruitment

Patients with AUD treated in the inpatient or outpatient psychiatric clinics of the Psychiatric University Hospital Charité at St. Hedwig-Hospital or Salus Clinic Lindow will be contacted by the study personal. If interested, they receive the study information and will be screened for eligibility during a short interview.

### Inclusion criteria

age: 18–65 yearsdiagnosis of alcohol dependence according to ICD-10 (F10.2)completed in-patient withdrawal treatment during the last 3 monthshistory of alcohol craving, confirmed via craving questionnairesable to provide written informed consent

### Exclusion criteria:

substance dependence other than alcohol and nicotinecurrent alcohol intoxication (randomly tested via measurement of breath alcohol concentration)unable to understand the study information, consent form or principles of the studyabstinence for less than 7 days or on-going consumption of alcoholsevere neuropsychiatric disorder, e.g., schizophrenia spectrum disorders, bipolar affective disorder or substantial cognitive impairmentserious illnesses influencing brain-/heart-function with influence on physiological study parameters.acute suicidality (or acute endangerment of others)concurrent pharmacological treatment targeting AUD (i.e. benzodiazepines) or craving (i.e. acamprosate, disulfiram, naltrexone, nalmefene) and further medication significantly influencing heart frequency.

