#### Outcomes

Primary outcomes of the study are changes in craving levels measured by psychophysiological parameters (HR, HRV with special focus on HF-HRV, EDA, pupillometry) and subjective parameters (VAS) before, during and after VR-exposure to alcohol-associated cues compared to neutral cues.

Secondary outcomes are a) changes in subjective and objective craving levels compared between the two VR-scenarios bar vs. living room, b) the changes of subjective craving over the following 3 h after VR-exposure, c) measures of the sense of presence (scores of IPQ), d) measures of motion sickness assessed with the Fast Motion Sickness Scale.

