#### Statistical methods

Statistical analyses are planned to be conducted using the software SPSS (SPSS Inc., Chicago, IL, United States). Growth-curve mixed models will be used to examine the effect of the three scenarios as within subject-condition (neutral, living room, bar) on physiological and subjective craving parameters. To address the change of subjective craving following the exposure, growth-curve mixed models will be used to examine the effect time (follow-up immediately, after 1, 2 and 3 h after VR exposure as within subject-factor with 4 levels) on craving levels as assessed by VAS.

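### Current intoxication is excluded, but the only objective check named is random breath testing, so an undeclared drinker can go untested into the VR session

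*Protocol article*

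**What the plan says.** Under Exclusion criteria, the protocol article rules out current intoxication and states how this is verified: "alcohol intoxication (randomly tested via measurement of breath alcohol". A separate criterion excludes abstinence "for less than 7 days or on-going consumption of" alcohol, with no objective check named.

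Under Recruitment, those approached are "Patients with AUD treated in the inpatient or outpatient psychiatric clinics" of the two sites, and they "will be screened for eligibility during a short interview". Under Inclusion criteria, in-patient withdrawal treatment must have been completed within the last 3 months.

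Under Outcomes, the primary outcomes are changes in "psychophysiological parameters (HR, HRV with special focus on HF-HRV, EDA, pupillometry) and subjective parameters (VAS"). The analysis under Statistical methods examines "the effect of the three scenarios as within subject-condition (neutral, living room, bar").

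The article already guards these outcomes against outside influences. It excludes serious illness that affects the physiological parameters, and "further medication significantly influencing heart frequency". No section provides a breath test for every participant before VR exposure.

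**The concern.** An exclusion criterion applies to every participant, whereas a random test checks only those it happens to reach. For anyone it misses, the barrier is what the patient says at interview. The article's own Background gives a reason not to lean on that: it faults self-rated craving because patients may give the socially acceptable answer. Admitting to recent drinking, when this means exclusion, is open to the same pressure.

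Two things are at stake. The first is eligibility and safety: a patient whom the protocol meant to keep out could undergo deliberate craving induction. The second is data quality. That acute alcohol acts on heart rate, HRV, skin conductance, pupil size and craving is general pharmacology and is not stated in the article. It does fit the article's own exclusion of intoxication and of illnesses and drugs that disturb these measures.

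**Working it through.** **1. Can the stated checks enforce the criterion?** The article names two checks: an interview for everyone and a breath test at random. A participant who has been drinking, denies it and is not selected for testing passes both. This follows from the text and needs no figures.

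**2. What does the within-subject design remove?** Each VR block lasts 5 min. Each neutral block comes directly before its target scenario, and there is a break of up to 45 min after the first target (VR exposure).
- A constant shift in level appears in both neutral and target blocks and cancels in the difference.
- A steady drift does not cancel fully. Neutral and target midpoints lie 5 min apart (2.5 and 7.5 min), so the neutral-versus-target contrast carries 5 min of drift, always in the same direction. The two target scenarios lie up to 5 + 45 + 5 = 55 min apart. Their order is randomized, so this averages out across participants but adds noise. The 3 h craving follow-up carries the most drift.
- Blunted or altered cue reactivity changes the contrast itself and does not cancel.

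**3. How many participants could be affected?** The article gives no rate of recent drinking, no share tested and no split between inpatients and outpatients. All three are assumed here.

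Outpatients only: expected undetected = outpatients × positive rate × (1 − share tested).
- 15 × 0.03 × (1 − 0.5) = 0.2
- 30 × 0.10 × (1 − 0.5) = 1.5
- 45 × 0.10 × (1 − 0.2) = 3.6

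All 60 participants: expected undetected = 60 × p × (1 − q), and the chance of at least one = 1 − [1 − p(1 − q)]^60, where p is the share intoxicated at the session and q the share tested.

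| Share tested (q) | p = 2% | p = 5% | p = 10% |
|---|---|---|---|
| 25% | 0.9 (60%) | 2.25 (90%) | 4.5 (99%) |
| 50% | 0.6 (45%) | 1.5 (78%) | 3.0 (95%) |
| 75% | 0.3 (26%) | 0.75 (53%) | 1.5 (78%) |
| 100% | 0 | 0 | 0 |

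The last row assumes an accurate test.

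**4. What would this do to power?** The plan's figure comes first. A two-sided paired t-test with d = 0.4 and alpha 0.05 has power 0.808 at n = 52 and 0.7999 at n = 51, so the stated n = 52 reproduces. Other settings also give 52, so this does not show which calculation was used, and the present point does not depend on it.

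Now suppose that a fraction c of participants is intoxicated and undetected, that they show no cue effect at all, and that the SD is unchanged. Then d becomes 0.40 × (1 − c).

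| c | d | Power at n = 52 |
|---|---|---|
| 0 | 0.40 | 0.81 |
| 2.5% | 0.39 | 0.79 |
| 5% | 0.38 | 0.77 |
| 10% | 0.36 | 0.72 |

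The largest count in step 3, 4.5 of 60, is 7.5% and falls between the last two rows.

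**The case against.** The strongest reply is that the article contains no contradiction. The exclusion covers every patient, everyone is interviewed, and the clinical assessments take about 90 min, so staff see each participant at length. On this view the random test is an extra safeguard. The word may also mean unannounced testing at random times, possibly of everyone. The share tested, timing and threshold are details that an article commonly leaves to the full protocol.

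Much of this stands. A reader might infer that the breath test is the only barrier; it is not, because the interview also screens. The missing share, timing and threshold are not faults of the article. What remains is the method that the article does state. Read plainly, a random test does not reach every participant. Even unannounced testing of everyone would not guarantee a test before the session.

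It can also be said that the numbers are wholly assumed. They are. The positive rate would have to apply to patients who have already passed the interview, and the high ends combine unfavourable inputs. The relapse rate of up to 85% cited in the article is a long-term figure and says nothing about the day of the session.

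**Conclusion.** The point holds as a weakness in how an eligibility criterion is enforced. The stated checks can let an undeclared, untested drinker into the VR session. Under assumed inputs the expected number is 0.2 to 4.5, roughly 0 to 4 of 60; the true number cannot be found from the article. The statistical effect is modest. Even if affected participants show no cue effect, 5% of them lowers power at n = 52 from 0.81 to 0.77. The stated sample size is not called into question.

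A reader might go further and infer that an undetected case makes the data invalid. The article does not support that. Each participant serves as their own control, a constant shift cancels, and the main contrast carries only about 5 min of any drift. The accurate statement is that the outcomes may be distorted through altered reactivity, through drift (above all in the 3 h follow-up) and through added noise. The case for changing the plan rests mainly on eligibility and safety, and on how little the change costs.

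**What to change.** In the Exclusion criteria, replace *randomly tested* with a breath alcohol test for every participant immediately before the VR session. Record the value, apply the existing exclusion to a positive result, and state how a missing result is handled in enrolment and analysis.

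The cost is at most 60 short tests with a method already in the protocol, plus an occasional rescheduled or excluded participant.

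A same-day breath test does not verify 7 days of abstinence. That criterion would still rest on self-report, and the article should say so. If *randomly* already means unannounced testing of everyone, correct the wording and state that a test is done before each session.

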### Data collection

#### Clinical data and questionnaires

General baseline data are collected in interviews before the VR exposure. These potentially confounding variables include demographic data (socioeconomic status), age, gender, medical history and comorbidities. Screening interviews include the Alcohol Urge Questionnaire (AUQ, [27]), Obsessive Compulsive Drinking Scale (OCDS, [28]) and Craving Automated Scale for Alcohol (CAS-A, [29]) to ensure the capability of perceiving and indicating subjective craving in patients. Severity of alcohol dependence will be measured with the Alcohol Use Disorder Identification Test (AUDIT, [30]), the Alcohol Dependence Scale (ADS, [31, 32]) and the Lifetime Drinking History (LDH, [33]). VAS scores (scores from 0–100)—the international standard measurement of subjective craving [34]—will be assessed before, during (3 times during each VR environment, minutes 00:30, 02:30, 04:30, 05:30, 07:30, 09:30, 10:30, 12:30, 14:30, 15:30, 17:30, 19:30) and directly after the VR exposure (min. 20:30). Furthermore, we will assess VR-specific side effects (kinetosis) using the Fast Motion Sickness Scale [35] during VR exposure. To study the short-term effects of VR exposure on craving, participants will indicate their craving level every hour for 3 h after exposure on a VAS and via the AUQ. To evaluate the feeling of “presence” during VR exposure, participants will be asked to complete the Igroup Presence Questionnaire (IPQ, [36, 37]) after completing VR exposure. The assessment of clinical data and questionnaires is estimated to take approximately 90 min. (Fig. 1; Workflow).

**Fig. 1 Fig1:**
[figure not shown]
Workflow CRAVE-study. Abbreviations: AUQ – Alcohol Urge Questionnaire, OCDS – Obsessive Compulsive Drinking Scale, CAS-A – Craving Automated Scale for Alcohol, AUDIT – Alcohol Use Disorders Identification Test, ADS – Alcohol Dependence Scale, LDH – Lifetime Drinking History, VAS – Visual Analogue Scale, HR – heart rate, HRV – heart rate variability, EDA – electrodermal activity

#### Psychophysiological data

To analyze the effect of VR exposure on craving-related physiological markers, we will assess heart rate (HR), heart rate variability (HRV), electrodermal activity (EDA) and pupillometry. Measurements will take place continuously during VR exposure conditions.

In order to collect cardiovascular (HR, HRV) and EDA data, we will employ the BIOPAC MP 160 system (Biopac Systems, Santa Barbara, CA, USA) together with a BioNomadix- RSPEC and 3-lead contact electrodes as well as the BioNomadix PPGED and a wireless remote sensor. The eye-tracker used to capture event-related pupil dilation is integrated into the VR headset (VIVE Pro Eye).

We will employ different preprocessing and analysis methods to extract HRV parameters in the time- (e.g., standard deviation of all interbeat intervals) and frequency domain (e.g., high/low frequency HRV). Here, we will use the AcqKnowledge® software provided by Biopac Systems and perform automated analyses of parameters of interest according to international measurement standards [38]. Tonic EDA will be measured with skin conductance level extrapolated via continuous decomposition analysis (CDA) [39]. HRV as well as EDA parameters will be averaged across the conditions (pre, post and during different exposure scenarios). Pupil diameter and blink rate during exposure scenarios will be analysed using algorithms by SomaReality (Soma Reality GmbH) [40].

#### VR exposure

The necessary hardware used for the VR exposure include a VR head-mounted display (HTC VIVE Pro Eye) and a desktop PC based on SCHENKER XR Station with Intel Core i5-12,500. Patients will be asked to indicate their drink of choice (schnaps, red wine, white wine, beer or vodka) and choose between different possible bars for the VR exposure (see suppl. material for further details). According to patient’s preference regarding their drinks and bar specifications the VR scenarios will be individualized to these characteristics. Subsequently, all patients start with a VR acclimation session (approximately 1 but up to 5 min.) with unspecific context (clean, white waiting room; Fig. 2A) in order to accustom to the VR experience, headset and biosensors to avoid an arousal reaction during the experimental VR session. The exposure starts in a neutral environment (baseline): a “non-room” (black room with an indicated horizon and a bright grid for spatial orientation; Fig. 2D). Next, patients are confronted with the first of two high-risk scenarios in a randomized order (target situations): a) sitting on a couch in a living room, alone, with their pre-selected drink on a couch table before them (Fig. 2C), b) being in their bar of choice (Fig. 2B and F) surrounded by other people where the bar-keeper serves their pre-selected drink, puts it on the table in front of the patient and tells them to enjoy it (Fig. 2E). After the first risk situation, patients stop the VR exposure for up to 45 min allowing craving to decrease. Then, they enter the neutral environment (“non-room”) again before being exposed to the second risk situation (living room/bar). The duration of exposure to each VR situation (both baseline conditions, bar and living room) is 5 min, resulting into an overall VR exposure of 20 min.

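### The break before the second neutral run has a cap but no minimum, no ending criterion and no craving rating, so residual craving can enter the neutral comparator and dilute the primary contrast

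*Protocol article*

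**What the plan says.** All places are in the protocol article.

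- **Sequence (VR exposure).** Acclimation comes first: "all patients start with a VR acclimation session (approximately 1 but up to 5 min". Its stated purposes include "to avoid an arousal reaction during the experimental VR session". A neutral run follows, and then: "Next, patients are confronted with the first of two high-risk scenarios in a randomized order (target situations".
- **Break (VR exposure).** "After the first risk situation, patients stop the VR exposure for up to 45 min allowing craving to decrease". Patients then enter the neutral room "again before being exposed to the second risk situation (living room/bar"). No second acclimation is described.
- **Durations (VR exposure).** "The duration of exposure to each VR situation (both baseline conditions, bar and living room) is 5 min", so four runs make 20 min.
- **Craving ratings (Clinical data and questionnaires).** VAS is taken "3 times during each VR environment, minutes 00:30, 02:30, 04:30, 05:30, 07:30, 09:30, 10:30", and so on to 19:30, with one further rating after exposure at 20:30.
- **Persistence of craving (Exploratory objectives).** One objective is to "assess craving duration over the first 3 h following the" exposure.
- **Analysis (Outcomes; Statistical methods).** The primary outcomes compare alcohol-associated with neutral cues. The model has a within-subject condition with three levels: neutral, living room and bar.

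**The concern.** The break is the washout of a within-patient sequence: neutral 1, first scene, break, neutral 2, second scene. Its stated purpose is to let craving fall, but the only rule given is an upper limit. Read literally, a 5-min break complies, and so does re-entry at 45 min with craving still raised. The protocol does not claim to know that craving has gone by then, since how long it lasts is one of the things it sets out to measure.

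Neutral 1 never follows an alcohol scene and neutral 2 always does. Randomisation concerns only which alcohol scene comes first, so it cannot balance carry-over into neutral. With the two neutral runs forming one level, any residual craving goes into the comparator of the primary outcome and pulls the contrast towards zero for measures that rise with craving. Break length and craving just before re-entry cannot be recovered later if they are not recorded.

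**Working it through.** **1. Where the ratings fall.** The VAS times run on a clock of VR time (4 × 5 = 20 min), which leaves the break out.

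| Run | VR time (min) | VAS |
|---|---|---|
| Neutral 1 | 0–5 | 00:30, 02:30, 04:30 |
| First scene | 5–10 | 05:30, 07:30, 09:30 |
| Break | not counted | none listed |
| Neutral 2 | 10–15 | 10:30, 12:30, 14:30 |
| Second scene | 15–20 | 15:30, 17:30, 19:30 |

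The first rating after the break is taken 30 s into neutral 2 and is itself neutral outcome data.

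**2. The plan's own figure.** Sample size gives n = 52 for d = 0.4, alpha 0.05 and power 0.8. An exact two-sided paired t calculation reproduces it: n = 52, power 0.808. The break plays no part in that calculation.

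**3. Residual craving (assumed model).** The documents give no decay rate. Assume exponential decay from the end of the first scene with half-life *h* of 10 to 40 min and break length *b*. As a share of the first-scene rise:

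- middle of neutral 2: r = 2^(−(b + 2.5)/h)
- middle of the second scene: s = 2^(−(b + 7.5)/h)

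Example, b = 5 and h = 10: r = 2^(−0.75) = 0.595 and s = 2^(−1.25) = 0.420.

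**4. Effect on the pooled contrast.** Let the true rise be Δ. Block 1 gives Δ. Block 2 depends on how the residual combines with the second scene.

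- *Same level:* the second scene reaches the level it would have reached anyway. Block 2 gives Δ(1 − r), and the average of the two blocks is Δ(1 − r/2). Loss = r/2.
- *Additive:* the residual also adds to the second scene. Block 2 gives Δ(1 − r + s). Loss = (r − s)/2.

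| b (min) | h (min) | r | s | Loss, same level | Loss, additive |
|---|---|---|---|---|---|
| 5 | 10 | 0.595 | 0.420 | 30% | 9% |
| 5 | 40 | 0.878 | 0.805 | 44% | 4% |
| 15 | 10 | 0.297 | 0.210 | 15% | 4% |
| 15 | 40 | 0.738 | 0.677 | 37% | 3% |
| 45 | 10 | 0.037 | 0.026 | 2% | 1% |
| 45 | 40 | 0.439 | 0.403 | 22% | 2% |

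**5. Consequence for power (illustration).** Take the same-level case, n = 52 and an unchanged SD of the contrast. Then d = 0.4 × (1 − r/2):

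- r = 0: d = 0.40, power 0.808
- r = 0.25: d = 0.35, power 0.697
- r = 0.50: d = 0.30, power 0.565

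**The case against.** **A condensed article.** The text can be read as a break that ends once craving has fallen, with 45 min as the limit. The workflow figure is not shown and the full protocol may hold the rule. This stands in part, and a 5-min break is only the most literal reading. But the article describes the break and lists the VAS times in detail, and the rule it gives does not secure its stated purpose. The remedy also goes beyond writing down a missing detail.

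**Carry-over will be visible.** The 10:30 rating works nearly as an end-of-break check, and physiology is recorded continuously during exposure. This stands for detecting carry-over in subjective craving. It does not prevent carry-over, and the three-level condition as described does not separate the two neutral runs.

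**A reader might infer that carry-over is established.** The documents do not support that. They give no decay rate and no distribution of break lengths, and the primary hypothesis is of a transient rise. Following craving for 3 h is a measurement plan and is not evidence that craving lasts that long. Breaks may run close to 45 min in practice.

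**A reader might infer that refitting the headset without a second acclimation adds to the same bias.** This is possible but not shown. By the break, patients have had acclimation and 10 min of VR. The direction may also differ by parameter. The Background says that HF-HRV reflects parasympathetic activity and is increased by alcohol cues. If arousal on re-entry lowered it in neutral 2, the contrast would widen.

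**A reader might infer that bar versus living room is biased.** Scene order is randomised, so each scene falls second equally often on average. Carry-over does not systematically favour one scene by position if both leave a similar residual. The main cost there is precision, through break lengths that vary between patients.

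**Conclusion.** The concern holds as an uncontrolled risk of unknown size to the primary target-versus-neutral contrast. It follows from three features together: a washout with only an upper limit, a second neutral run that always follows an alcohol scene, and a neutral condition modelled as one level.

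The range is wide and rests on assumed half-lives of 10 to 40 min. Additive carry-over costs about 1% to 9% of the pooled contrast, which is minor. The 30% to 44% loss needs two further assumptions: a 5-min break for every patient and a second scene that reaches the same level whatever the residual. Even a 45-min break leaves a loss of 2% to 22% in that case, so these calculations do not show any particular length to be sufficient. The change is worth making because it is cheap and the missing measurements cannot be obtained afterwards.

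**What to change.** 1. Use one break length for all patients, chosen by the sponsor within the existing cap, and record the actual length for each patient. The documents do not support any specific value, and none is proposed here.
2. Take a VAS rating at the start and at the end of the break.
3. Keep neutral 1 and neutral 2 distinct in the model, either by comparing each scene with its own preceding neutral run or by adding a period term.
4. Report the first-block contrast (neutral 1 versus first scene), which is free of this carry-over, beside the pooled contrast.
5. Optionally, repeat the short acclimation before neutral 2.

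**Cost.** Sessions become somewhat longer for patients who would have had a shorter break. Each patient gives two more VAS ratings, and a repeated acclimation would add about 1 to 5 min. The first-block estimate uses half of the runs and is less precise than the pooled one. Items 3 and 4 need no extra data.
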